### Safety

Safety assessments will be based on adverse event reports and vital signs. At every visit, adverse events and vital signs will be recorded. The major indicators for vital signs include breath, temperature, systolic blood pressure, diastolic pressure, pulse, and so on. Generally, any unexpected symptom, vital sign or sickness, as long as they cause discomfort, shall be recorded as an adverse event. The starting date, the ending date, the degree, the relations with the trial medicine, and whether they drop out of the study should be recorded correspondingly. If necessary, the patients will receive relevant treatment. If the adverse event still exists, the follow-up will go on until the adverse event disappears.

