**Figure 1 F1:**
[figure not shown]
Trial design.

**Table 1 T1:** Calendar summary

**Period**	**Screening**	**Washout**	**Treatment**				**Follow-up**
**Week(W)**	**-1 W**	**0 W**	**1 W**	**2 W**	**3 W**	**4 W**	**4th week after the end of treatment**
Inclusion and exclusion criteria	×						
Informed consent	×						
Demography	×						
Past Medical history & treatment history	×						
Spiegel Scale	×	×					
Self-rating Anxiety Scale	×	×				×	
Beck Depression Inventory	×	×				×	
http://Pittsburgh Sleep Quality Index	×	×	×	×	×	×	×
CM syndromes and signs	×	×	×	×	×	×	×
Sleep diary	×	×	×	×	×	×	
Prescription (include every herb and dose)			×	×	×	×	
Vital signs	×	×	×	×	×	×	
Adver event		×	×	×	×	×	

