### Secondary efficacy indicators

The secondary efficacy indicators include sleep onset latency, wake time after sleep onset, sleep efficiency, Pittsburgh sleep quality index (PSQI) and CM symptoms and signs. Sleep onset latency, wake time after sleep onset and sleep efficiency are obtained from the sleep diary. The Chinese-version PSQI is employed to measure the quality of sleep. The PSQI is a self-rated questionnaire used to assess sleep quality and disturbances over a 1-month time interval. Nineteen individual items generate seven component scores: subjective sleep quality, sleep latency, sleep duration, habitual sleep efficiency, sleep disturbances, use of sleeping medication, and daytime dysfunction.

Many studies have demonstrated that the Chinese-version PSQI is a sensitive, reliable, and valid tool to assess the quality of sleep [18,19]. In addition, CM symptoms and signs will be assessed. The main symptoms and signs include headache, dizziness, spontaneous sweating, night sweating, dreaminess, amnesia, anorexia, lassitude of spirit and lack of strength, oppression in the chest, daytime sleepiness, irritability, palpitations, epigastric fullness, tinnitus, thirst, bitter taste in the mouth, abundant sputum, yellow urine, dry stool, sloppy stool, pulse condition, and tongue manifestation.

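### The Safety section records an event as adverse only if it is unexpected and causes discomfort, so applied as written the adverse event counts can be too low

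*Protocol article*

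**What the plan says.** The Safety section of the protocol article names two sources: "Safety assessments will be based on adverse event reports and vital signs". On timing it says "At every visit, adverse events and vital signs will be recorded", and on content "The major indicators for vital signs include breath, temperature, systolic blood pressure, diastolic pressure, pulse, and so on". It then gives the rule for what counts as an adverse event: "any unexpected symptom, vital sign or sickness, as long as they cause discomfort, shall be recorded as an adverse event". That sentence opens with the word *Generally*.

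For each event so recorded, the section asks for start and end dates, degree, relation to the trial medicine, and whether the patient leaves the study. An event that persists is followed until it has gone.

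Table 1 marks vital signs from screening to week 4 and adverse events from washout to week 4. It marks the row "CM syndromes and signs" at every time point, follow-up included.

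The section on secondary efficacy indicators uses that checklist as an outcome: "The secondary efficacy indicators include sleep onset latency, wake time after sleep onset, sleep efficiency, Pittsburgh sleep quality index (PSQI) and CM symptoms and signs". It continues: "The main symptoms and signs include headache, dizziness, spontaneous sweating, night sweating, dreaminess, amnesia, anorexia". The rest of the list includes daytime sleepiness, palpitations, epigastric fullness and sloppy stool.

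**The concern.** Whether an event was expected, and whether the patient felt it, are judgements about an event. They are properly made once it is on record. Here they decide whether it goes on record at all.

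The comparison at stake is between three herbal groups and placebo, in a study whose stated purpose is to speed the development of new CM drugs. If untoward events are screened out at entry, the adverse event table understates harm and cannot be repaired afterwards: nobody will have recorded the degree or the relation to treatment of the events left out.

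The checklist adds an uncertainty. Several of its items could be harms as easily as symptoms of the condition, and the article does not say what happens when one of them appears or worsens on treatment.

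**Working it through.** No arithmetic applies. The article states no adverse event rate, no safety sample size and no safety power. The check is to put the rule beside the other statements and follow each kind of event through it.

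1. **The rule as written.** An event is recorded as adverse if it is (a) unexpected and (b) causes discomfort. Failing either test keeps it out.

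2. **An abnormal vital sign without symptoms.** Take a patient whose blood pressure is raised at the week 2 visit and who feels nothing. Patients with hypertension are excluded at entry, so this would be a new finding. Test (b) fails, so there is no adverse event. The reading itself is kept, because vital signs are recorded at each treatment visit without any discomfort condition. What is missing is the rest: onset and end dates as an event, degree, relation to the trial medicine, and follow-up to resolution. The last is not made good by the visit schedule, since Table 1 marks no vital-sign measurement after week 4. The rule also works against itself: it names vital signs as something that can be an adverse event, then adds a condition that a change in blood pressure or pulse may well not meet.

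3. **A foreseeable but untoward effect of the herbs.** Suppose a patient has an uncomfortable effect that staff regard as typical of the prescription. Test (a) fails, so no adverse event is recorded. The filter is not needed for judging causality, because relation to the trial medicine is already recorded for each event. It is also hard to apply evenly. Prescriptions are individual and may change at each visit, the efficacy assessor is blinded, and the article gives no reference for what is to be expected.

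4. **A checklist symptom.** The list has 20 symptoms, plus pulse and tongue findings. A patient without palpitations at week 0 who reports them at week 2 has an unexpected and uncomfortable symptom, so both tests are met and the rule records it. Nothing in the article excludes it, and nothing confirms that it is to be recorded. The efficacy label together with the word *unexpected* leaves room for staff to score it as efficacy only.

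5. **Size.** Suppose a fraction *f* of untoward events fails one test or the other. The recorded count is then the true count × (1 − *f*). The article gives neither quantity, so *f* could lie anywhere from 0 upward, and it could be the same or different across the four groups.

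**The case against.** The strongest reply is that the sentence is a summary in loose English. It begins with *Generally*, and *unexpected* may simply mean untoward. The article sets up no list of expected reactions that could be subtracted. Operational definitions belong in the full protocol, which is not shown. No stopping or group-selection rule uses adverse event counts, since early stopping rests on total sleep time alone. The study also calls itself exploratory and plans a further trial.

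Much of this is fair and limits the point. It does not remove it. The article does not leave the definition out; it states one, and that definition has two conditions that should not be there. If *untoward* was meant, the sentence should say so. The discomfort condition has no such innocent reading.

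Three stronger readings are tempting, and the documents do not support them.

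- **That vital-sign harm goes unseen.** It does not. Vital signs are a second, parallel safety source, and the weekly values will be in the data.
- **That every checklist symptom is lost to safety because patients are asked about it at each visit.** Being asked about a symptom does not make its appearance expected in a given patient, and no section bars it from adverse event recording.
- **That a real excess on herbs disappears.** Suppose, purely as an assumption, that 20% of herb patients and 5% of placebo patients have a new checklist symptom, and that 5% in each group have some other event. The true rates are then about 20% + 5% = 25% against 5% + 5% = 10%. They shrink to 5% against 5% only if every checklist event goes unrecorded. If all are recorded, the 15-point difference stands in full. The rates are invented, and the extreme case needs the unsupported reading just above. Nor does the article show that losses would fall mainly on the herbal groups: one rule applies to all four, with patients, clinicians and assessors blinded.

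It is also fair to resist entering every worsened checklist item automatically. Dreaminess, irritability, daytime sleepiness and tongue or pulse findings fluctuate or lie close to insomnia itself, and could dilute the comparison.

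**Conclusion.** The point holds as a defect in a stated definition. Unexpectedness and discomfort act as entry conditions. Symptom-free vital-sign abnormalities and foreseeable but untoward effects of the herbs therefore fall outside the adverse event count, and outside the recording of dates, degree, relatedness and follow-up to resolution.

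Adverse event counts can be too low as a result. This is a risk created by the wording, not a demonstrated shortfall. Its size, and whether it differs between groups, cannot be worked out from the article. The conclusion assumes that staff apply the sentence literally; if they read *unexpected* as untoward, only the discomfort condition does harm. The matter should be corrected, but it does not affect the primary efficacy comparison.

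**What to change.** Replace the definition in the Safety section with one to this effect: an adverse event is any untoward new or worsened symptom, sign, vital-sign abnormality or illness from the washout period onward, whether or not it is expected, causes discomfort or is thought related to the trial medicine. Record expectedness, discomfort and relatedness afterwards, as attributes of the event.

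Add one sentence stating that being an efficacy item on the CM checklist does not exempt a new or clearly worsened symptom from adverse event recording. This does not require every fluctuation of a checklist item to be entered.

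The change costs some wording and a small addition to the adverse event form. Vital signs and the checklist are already collected at every treatment visit, and Table 1 already starts adverse event recording at washout. The downside is more entries to process and raw counts that look less favourable.

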### Statistical methods

#### Sample size

The study is supposed to explore the daily clinical practice of three prestigious Chinese clinicians in primary insomnia treatment and to figure out the effective drug patterns prescribed by them. However, it is very difficult to estimate the sample size because of lack of a previous relevant study. To obtain expected results with a minimal sample size, a sequential design will be employed. The interim analysis will be conducted when the total number of patients having completed the study reaches 80 and 160 separately, for which we set up the early stopping criteria. The interim study can be treated as final if the difference in TST changes from baseline at 4 weeks between the CM and placebo groups is >0.5 hours and has statistical significance with *P* <0.05. When the early stopping criteria are met, the placebo group and the non-effective group will be dropped. The subsequent study will only focus on the effective group to explore the core drug patterns. If the number of effective patients is not sufficient to determine the core drug patterns, the recruitment procedure has to continue. The core drug pattern analysis shall be carried out every time the increment of new enrollment reaches 30 until the core drug patterns are obtained and kept constant.

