**Methods/design:**

A triple-blind, randomized, placebo-controlled, parallel-group clinical trial will be performed. Three clinicians will diagnose and treat every eligible patient individually and independently, producing three prescriptions from three clinicians for every patient. Patients will equally be randomized to one of four groups – medical group A, medical group B, medical group C, or placebo group – and observed for efficacy of treatment. The sample will include primary insomnia patients meeting DSM IV-TR criteria, Spiegel scale score >18, and age 18 to 65 years. A sequential design is employed. Interim analysis will be conducted when between 80 and 160 patients complete the study. The interim study could be stopped and treated as final if a statistically significant difference between treatment and placebo groups can be obtained and core effective drug patterns can be determined. Otherwise, the study continues until the maximum sample size reaches 300. Treatment of the CM group is one of three Chinese clinicians’ prescriptions, who provide independently prescriptions based on their own CM theory and the patient’s disease condition. Assessment will be by sleep diary and Pittsburgh sleep quality index, and CM symptoms and signs will be measured. Primary outcome is total sleep time. Assessment will be carried out at the washout period, weeks 1, 2, 3, and 4 and 4th week after the end of treatment. Effectiveness analysis will be per intent to treat. A multi-dimension association rule and scale-free networks method will be used to explore the effective core drug patterns.

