### Primary efficacy indicator

#### Total Sleep Time (TST)

In this study, the major indicator is the total sleep time (TST), which is assessed according to the sleep diary. All patients are required to record their sleeping information in detail every day. The sleep diary contains the following information: the time a patient goes to bed and gets out of bed; the time a patient thinks sleep onset occurs; the presumed cause, number, time, and length of any nighttime awakenings and activities during these moments; the name, dosage and time of any drugs used, including medication, sleep aids, caffeine and alcohol, and so forth; and activities happening 3 hours before bedtime, such as meditation, watching television, playing PC games, exercise, and so forth.

The efficacy can be confirmed only when improvement in TST is >0.5 hours and is considered statistically significant. Normally, the participants are not allowed to take any pharmacologic medicine used to treat insomnia. However, they are allowed to do so if they could not bear the bitterness brought about by insomnia. Under such circumstances, the dosage and the name of the medicine must be recorded carefully in sleep diaries.

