### Analysis strategy

The analysis will be per intent to treat. The mean and standard deviation shall be applied to the continuous variables, and percentages to the categorical variables. For comparison of two independent samples, the *t* test and analysis of variance will be applied for continuous variables and the chi-square test for categorical variables. In addition, nonparametric tests will also be applied for analysis. The efficacy for patients taking any pharmacologic medicine will be assessed using the method of last observation carried forward.

As mentioned above, the exploration analysis on core drug patterns will only be based on the effective patients in order to guarantee the efficacy of the explored core prescription. The patients’ syndrome and signs, CM patterns and the treatment effect shall be considered during the analysis. The core drug pattern can be concluded from the combination of high correlation and frequency. The core drug patterns must confirm to the CM theory and be accepted by the prestigious Chinese clinicians. The multi-dimension association rule and scale-free networks method will be applied to mine the core drug patterns and drug utilization rule of three Chinese clinicians [15,20-22]. In CM, the disease syndromes and signs, disease pattern and treatment are a dynamic procedure. The disease pattern varies with syndromes and signs. As a result, the treatment varies with the pattern of disease. So we not only explore the core drug patterns of different prestigious Chinese clinicians, but also mine the core drug patterns corresponding to different syndrome combinations and disease patterns.

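### Both interim looks use an unadjusted P<0.05 with a 0.5 h hurdle for three clinician arms sharing one placebo: if all are inert, the chance of declaring at least one effective by the second look is about 8–10% at an SD of 1 h or more

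*Protocol article*

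**What the plan says.** The Sample size section of the protocol article calls the design sequential and sets two looks: "The interim analysis will be conducted when the total number of patients having completed the study reaches 80 and 160 separately". The rule at each look is that "The interim study can be treated as final if the difference in TST changes from baseline at 4 weeks" passes a two-part test of CM against placebo: more than half an hour, and a P value below 0.05. Once this is met, placebo and any group found non-effective are dropped, and later work uses only the effective group.

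The abstract describes the timing differently, "Interim analysis will be conducted when between 80 and 160 patients complete the study", and adds "Otherwise, the study continues until the maximum sample size reaches 300". It also makes stopping depend on the core drug patterns being determinable.

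The Total Sleep Time section repeats the two-part condition without a level: "The efficacy can be confirmed only when improvement in TST is >0.5 hours and is considered statistically significant". The Randomization section allocates patients equally to clinician groups A, B and C and placebo.

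**The concern.** A significance level of 0.05 holds for one comparison at one look. This plan applies it at two looks, and probably at a third, and to three arms that share a placebo. Each extra opportunity adds to the chance that at least one inert arm passes.

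The consequence is large because a pass ends the placebo comparison. It also labels a clinician's prescriptions effective, and the core-pattern search then uses only patients counted as effective. A false positive therefore enters everything that follows, with no control group left to expose it.

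The boundary is stated in the article. It is not a detail left to an analysis plan.

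**Working it through.** **What there is to reproduce.** The article states no overall type I error, power or derived sample size. Its only figure is P<0.05. As a check, one clinician at one look gives 2.5% in the CM-favouring direction, as it should for a two-sided 5% test.

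**Inputs from the article.** Equal allocation to four arms; looks at 80 and 160 completers (80/4 = 20 and 160/4 = 40 per arm); maximum 300 (300/4 = 75 per arm); P<0.05 and a difference above 0.5 h; t test (Analysis strategy).

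**Assumptions.** Two-sided P; three separate comparisons with placebo; P<0.05 also at 300 where that look is counted; SD of the change in TST not given, so 0.5 to 2.0 h is shown.

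**When the 0.5 h hurdle matters.** The smallest significant difference is t × SD × √(2/n). At SD 1.0 h:
- n = 20: 2.024 × 1.0 × √(2/20) = 0.640 h
- n = 40: 1.991 × 1.0 × √(2/40) = 0.445 h
- n = 75: 1.976 × 1.0 × √(2/75) = 0.323 h

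The hurdle is stricter than the test only when SD is below 0.5/0.640 = 0.78 h at the first look, 0.5/0.445 = 1.12 h at the second, and 0.5/0.323 = 1.55 h at the third. Above those values it gives no protection.

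**Error rate with all arms inert.** Simulation of 400,000 trials with two-sample t tests against a shared placebo and the full two-part rule. Rates are cumulative, in the CM-favouring direction; the nominal rate is 2.5%.

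| SD (h) | Any of 3 by 80 | Any of 3 by 160 | Any of 3 by 300 (level inferred) | One given clinician by 300 |
|---|---|---|---|---|
| 0.5 | 0.2% | 0.2% | 0.2% | 0.1% |
| 0.67 | 2.4% | 2.5% | 2.5% | 0.9% |
| 0.8 | 5.0% | 5.3% | 5.3% | 2.1% |
| 1.0 | 6.3% | 8.0% | 8.1% | 3.3% |
| 1.25 | 6.3% | 10.1% | 10.8% | 4.4% |
| 1.5 | 6.3% | 10.2% | 12.6% | 5.3% |
| 2.0 | 6.3% | 10.2% | 13.4% | 5.7% |

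At SD 0.8 h a normal approximation gives 6.4% instead of 5.3%; elsewhere the choice matters little. The last column ignores that another arm's success would end the comparison, so it is slightly high.

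**Ratios to nominal.** Any of three by the second look: 8.0/2.5 = 3.2 at SD 1.0 h and 10.2/2.5 = 4.1 at SD 1.5 h. One given clinician: 3.3/2.5 = 1.3 to 5.7/2.5 = 2.3.

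**Pooled alternative.** One test of all CM patients against placebo over three looks gives about 2.4% at SD 1.0 h (2.6% in a separate calculation) and 5.6% at SD 2.0 h.

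**The case against.** - **The rule has two parts.** A reader might treat P<0.05 as the only boundary, or count both directions and reach about 27%. Neither is supported. The 0.5 h condition is part of the rule, and an arm worse than placebo cannot meet it. With the hurdle, inflation runs from none to roughly five times nominal, depending on an SD the article does not state.
- **The high multiples are not for one prescriber.** They are any-of-three rates. For a given inert clinician the ratio is at most about 2.3. This stands.
- **Two premises are inferred.** The level at 300 is not given, but about 8% to 10% is reached by 160 completers on the stated level alone. Separate tests are not stated outright, and the wording could mean pooled CM against placebo. A pooled test, however, could not identify a non-effective group to drop.
- **The look could be timed after seeing the data.** The abstract's range might suggest this, but the body fixes two looks. What remains is a wording conflict to correct.
- **"In addition, nonparametric tests will also be applied for analysis" might suggest a choice of test.** It is a general statement, and naming the primary test is ordinary analysis-plan detail. No point is made of it.
- **The study is exploratory.** The Discussion says so when defending a diary outcome, and a further randomized trial is planned. That lowers the consequence. It does not remove it, because the article also says when efficacy counts as confirmed and claims to have strictly tested it. Adjusting across distinct treatments in a screening trial can be debated; adjusting for repeated looks cannot.

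**Conclusion.** The concern holds in a limited form. The stated rule controls neither repeated looks nor three comparisons. On the separate-arms reading, the chance of at least one false declaration by the second look is about 8% at SD 1.0 h and about 10% at SD 1.25 h or more, against 2.5%. If P<0.05 is also used at 300, it is about 8%, 11%, 13% and 13% at SD 1.0, 1.25, 1.5 and 2.0 h. At SD 0.8 h it is about 5% to 6%, and below about 0.67 h there is no inflation because the hurdle dominates.

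These figures rest on equal arms, two-sided tests and an assumed SD. They do not show that each inert clinician faces several times the nominal rate. The two accounts of look timing also contradict each other and must be reconciled. This should be fixed; the exploratory aim and the planned later trial keep it from being more serious than that.

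**What to change.** 1. State that the comparisons are each clinician group against placebo.
2. Fix the looks at exactly 80 and 160 completers with a final analysis at 300, give the level for each, and correct the abstract to match.
3. Keep the 0.5 h condition.
4. Replace P<0.05 with group-sequential boundaries adjusted for three comparisons. Two-sided P<0.001 at 80 and 160 and P<0.0175 at 300 gives a simulated family-wise error of 2.5% in the CM-favouring direction before the hurdle is counted. An O'Brien-Fleming type set of about 0.000005, 0.0012 and 0.018 gives 2.4%.

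**Cost.** The wording changes and early stops become rarer. At SD 1.25 h, the difference needed at the first look under P<0.001 rises from 1.96 × 1.25 × √(2/20) = 0.78 h to 3.29 × 1.25 × √(2/20) = 1.30 h (normal approximation). At 300 the critical difference is 2.376 × 1.25 × √(2/75) = 0.485 h, below the 0.5 h already required. The final test therefore costs nothing while SD is at most 0.5/(2.376 × √(2/75)) = 1.29 h.
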